**Fig. 2 Fig2:**
[figure not shown]
Evaluation phases of the LHSI program

The evaluation of the project will include the following principles of the RE-AIM framework to:Deliver the graduate certificate courses using evidence-based knowledge and skill development strategies through workshop and online delivery.Explore how co-designed innovation programs can motivate students to achieve competence and confidence in innovation implementation within their health service.Evaluate the implementation and efficacy of the Leading Health Services Innovation program throughout each phase of the project.

### The study setting and population

Our partner is one of the largest public hospital and health services (HHS) in the Southern Hemisphere, comprising the full scope of health services, including quaternary and tertiary hospitals, community-based health services and aged care. It is a statutory body governed by a board of directors and is a recognized leader in the provision of world-class healthcare, with expertise in numerous specialties that provides the leverage to expand and drive healthcare forward through research, technologies, and partnership opportunities.

The Academic Team comprises experts from the health services management and health economics disciplines.

Research priorities include knowledge translation and health services innovation through the delivery of an innovative program to connect clinical and business decision-making. The health workforce from this health service and from other Queensland Health Hospital and Health Services have the opportunity to undertake the newly codesigned Graduate Certificate in Health Services Innovation.

### Study design

A mixed methods hybrid type 2 [35] clinical effectiveness and implementation trial was adopted for this study. This method is designed for dual testing of clinical intervention (workforce education) and implementation strategy (academic detailing). Direct blending of clinical effectiveness and implementation research aims to improve the speed of knowledge creation and support rapid translation. This hybrid design is motivated by the acknowledgment that traditional effectiveness studies tend to produce effectiveness estimates that are notably different from, and often worse than, the estimates obtained from efficacy studies [35]. The reason for this difference is attributed to the fact that effectiveness studies are frequently conducted under challenging, often “worst case”, conditions. These conditions include limited or no support from the research team during delivery and implementation, a lack of clear understanding about fidelity barriers, and a failure to make efforts to overcome these obstacles. In essence, the hybrid approach addresses these shortcomings and improves the accuracy of effectiveness estimates by incorporating elements from both efficacy and effectiveness studies. In the current hybrid type 2 study, the implementation intervention strategy (health workforce-led improvements) will be evaluated alongside and in support of the codesigned graduate certificate program. This creates a “medium case”, or “pragmatic”, set of delivery and implementation conditions that lie between the best and worst cases, which acknowledges that in real-world applications, studies often encounter a mix of challenges and support.

### Sample size

Primary users of the program are the Hospital and Health Service (HHS) health workforce, defined as practitioners and administrators who are trained by the project team (i.e., administrative support officers, nurses, medical practitioners, allied health) and who are enrolled in the graduate certificate. The two cohorts will commence the program one year apart. Each cohort will consist of staff selected by the HHS with up to forty (40) places per cohort. Cohort 1 commenced July 2023 in the LHSI program, which consists of the Graduate Certificate of Health Services Innovation, three roundtables, and a yearly conference. Cohort 2 commences in July 2024.

### Ethics

Ethical approval for this study was obtained from Griffith University (GU Ref No: 2023/566) and the Townsville Hospital Human Research Ethics Committee (HREC/2023/QTHS/100088). This research is considered negligible risk; however, the following key ethical issues have been identified: informed consent and power dynamics; and confidentiality [37, 38]. Informed consent and power dynamic is provided by the participants in the study where they will sign the purposefully designed consent form prior to the commencement of the interviews. The consent form will be contextualized to prevent participants feeling threatened by the format of a standard consent form. In addition, a participant information letter will be provided, outlining the purpose of the study, financial implications, confidentiality, consent implications and support network. Confidentiality is established by the researchers in order to protect the privacy of the individual participant and participating organisations. By using aggregated results in published work, and de-identification of organisations and participants, confidentiality will be maintained. Informed consent will be obtained from all participants prior to any involvement in the study. Consent for online anonymous surveys will be implied by the respondent completing the survey.

### Codesign stakeholder group protocol

Program development procedures, materials and assessments will be discussed at regular meetings with a stakeholder group that represents alumni of a previous graduate certificate program undertaken by the HHS, HHS executive and research practitioners, HHS experts and educators, healthcare practitioners, health services and health economics academics, learning and teaching curriculum development experts and the HealthInnTrans network (health sector experts).

### Data collection and analysis

#### Qualitative methods

According to the stage of the project, qualitative interviews will be conducted to identify a) workforce strengths and needs, b) current barriers to healthcare improvements, c) the value of the educational program and each course, d) the efficacy of knowledge translation, and d) satisfaction with the program. A thematic analysis of the interview transcripts and observation narratives will be used for its iterative process of making sense of the data [39]. Themes will be derived from the coded data, this process will be undertaken by two researchers independently. Information will be gathered regarding the intervention’s content, structure, operational methods and any potential changes over time. In addition, the experiences of healthcare professionals, along with facilitators and barriers will be explored. These analyses will provide insights to the projects aims and will assist with quality improvement of the program delivery, educational modules, and fidelity beyond the research project.

#### Quantitative methods

The National Health Service (NHS) Creating a Culture for Innovation tool [40] will be administered at three timepoints: at the start of the program, at the conclusion of the four courses of the Graduate Certificate and at 12 months post completion for each cohort.

In addition, an adapted version of the Academic Behavioral Confidence (ABC) Scale and the General Causality Orientations Scale (GCOS) [41] will be used at the beginning and end of each of the Graduate Certificate programs for both cohorts 1 and 2 (30–40 participants per cohort) (Fig. 2). The sample size will be restricted by the number of individuals enrolled in the Graduate Certificate. The ABC scale measures constructs of self-concept and self-efficacy and is a psychometric means of assessing the confidence that students have in their own anticipated research skills and study behaviors in relation to their degree program. The understanding that students have of their research skills can be important for making sense of their expectations of teaching, learning and assessment [42, 43]. The adapted ABC scale consists of 10 items that will allow for responses on a 5-point Likert scale. Data analysis will involve descriptive statistics to summarize the data collected from the NHS Creating a Culture for Innovation tool, the Academic Behavioral Confidence (ABC) Scale, and the General Causality Orientations Scale (GCOS). Changes over time will be examined by comparing results across the three timepoints for the NHS tool and between the beginning and end of the Graduate Certificate programs for the ABC and GCOS scales. Paired t-tests or repeated measures ANOVA will be conducted to assess any statistically significant differences in motivation and confidence levels across the timepoints [44]. Additionally, correlation analyses may be performed to explore relationships between participants' self-efficacy, confidence, and motivation in relation to research and innovation skills. The data collected from these instruments will be used to assess the motivation and confidence levels of the participants in relation to research skills, specifically innovation and implementation, skills and knowledge.

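### The plan reads the NHS Creating a Culture for Innovation tool as participants' motivation and confidence, and it is the only scale with a wave after the program ends

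*Protocol article*

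**What the plan says.** All of this stands in the protocol article under Quantitative methods, except where noted.

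- **Schedule of the NHS tool.** "The National Health Service (NHS) Creating a Culture for Innovation tool [40] will be administered at three timepoints". For both cohorts alike, the occasions are "at the start of the program, at the conclusion of the four courses of the Graduate Certificate and at 12 months post completion for each" of them.
- **Schedule of ABC and GCOS.** Change is to be compared "between the beginning and end of the Graduate Certificate programs for the ABC and GCOS scales", so there are two occasions.
- **Descriptive analysis.** Descriptive statistics will "summarize the data collected from the NHS Creating a Culture for Innovation tool, the Academic Behavioral Confidence (ABC) Scale, and the General Causality Orientations Scale".
- **Test.** "Paired t-tests or repeated measures ANOVA will be conducted to assess any statistically significant differences in motivation and confidence levels across the timepoints".
- **Interpretation.** "The data collected from these instruments will be used to assess the motivation and confidence levels of the participants in relation to research skills". The sentence goes on to specify skills and knowledge in innovation and implementation.
- **Constructs.** ABC is described as measuring self-concept, self-efficacy and students' confidence. Neither the NHS tool nor GCOS is given a description of what it measures.
- **Cohorts (Sample size).** "The two cohorts will commence the program one year apart": Cohort 1 in July 2023, Cohort 2 in July 2024. The first Study design section gives the Graduate Certificate a part-time length of two years.
- **Outcome framework (Table 1).** Quantitative confidence and motivation are listed under Effectiveness. No culture outcome is named, and the NHS tool does not appear in the table.

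**The concern.** The interpretation sentence follows a list of three instruments and gives all of them one construct, located in the individual participant. A tool whose title concerns a culture would ordinarily be taken to describe the setting in which the respondent works. A change in such a score is not evidence that the respondent became more or less confident or motivated.

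The schedule makes this matter. The only measurement after the end of teaching is made with the NHS tool. If the stated rule is followed, a report that confidence or motivation was maintained a year after the program would be drawn from that tool and no other. Confidence and motivation are listed as Effectiveness outcomes, so the mislabelling reaches what the trial may claim about effect.

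This differs from a detail that an article leaves to a fuller plan: the article states how the data will be read, and that statement is not supported by anything else in it.

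**Working it through.** The article gives no power, effect size, standard deviation or significance level for these scales, so there is no figure of the plan to reproduce. The check sets the statements side by side and adds date arithmetic.

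**Step 1. Which instruments the interpretation covers.** The descriptive-analysis sentence names all three. The interpretation sentence refers back to the instruments as a group, and no sentence between them removes the NHS tool. Read literally, all three are covered.

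**Step 2. What each instrument is said to measure, and when.**

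| Instrument | Construct described in the article | Start | End of program | One year after completion |
|---|---|---|---|---|
| NHS tool | none (title: culture for innovation) | yes | yes | yes |
| ABC | self-concept, self-efficacy, confidence | yes | yes | no |
| GCOS | none | yes | yes | no |

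**Step 3. What a conclusion about lasting change would rest on.** Scales with a wave after completion: 1 of 3, the NHS tool. Scales described as measuring confidence: 1 of 3, ABC. The two do not overlap. No scale that the article describes as measuring confidence is taken after the program ends.

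**Step 4. Calendar.** Inputs: starts in July 2023 and July 2024; program length 24 months; last wave 12 months after completion. The end of the four courses is taken as completion.

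- Cohort 1: July 2023; + 24 months = about July 2025; + 12 months = about July 2026.
- Cohort 2: July 2024; + 24 months = about July 2026; + 12 months = about July 2027.
- Overlap: July 2023 to July 2024 = 12 months, so Cohort 2's first wave falls 12 of 24 months into Cohort 1's program.

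The overlap is a fact about dates. To turn it into a bias, one would need to know how far Cohort 1 had changed the culture that Cohort 2 rates by July 2024. The article gives nothing on this, and no change at all is possible.

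**The case against.** **The tool's content is unseen.** The article does not describe its items, respondents or scoring. The culture reading comes from the title alone. This stands, and the point must carry it as an assumption. It also works the other way: the article offers no basis for reading the tool as individual confidence or motivation.

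**The sentence may be loose and collective.** It continues beyond confidence to skills and knowledge, and could mean what the battery as a whole informs. The schedules are kept apart by instrument, and Fig. 2, which is not shown, may map instruments to outcomes. This is a fair reading of intent and keeps the point modest. It does not remove the literal statement, which a later analyst would be entitled to follow.

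**The test sentence does not settle the matter.** A reader might infer that repeated measures ANOVA can only be meant for the NHS tool, since only it has three waves. That does not follow: with two occasions the ANOVA is valid and equivalent to the paired t-test, so the tests could be meant for ABC and GCOS alone. The point therefore rests on the interpretation sentence.

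**The staggered start is not an error.** Each cohort is measured at its own start, which is the right pre-program score for a within-participant comparison. No section calls Cohort 2's first wave a baseline for the organisation, plans to pool the cohorts or plans to compare them. This stands in full.

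**Conclusion.** The point holds as a mismatch between instrument and stated construct. The plan assigns NHS tool data to participants' motivation and confidence without support in its own text, and that tool alone supplies the wave a year after completion. The consequence is one of interpretation: any claim of lasting confidence or motivation from these scales would rest on an instrument whose title concerns culture. It assumes that the title describes the content.

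The 12-month overlap between the cohorts is a caveat only. The size and direction of any effect on Cohort 2's NHS scores cannot be computed from the document.

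Stronger readings are tempting but not supported:

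- **A known share of Cohort 1's effect already sits in Cohort 2's first score, or dilutes a pooled change.** The article gives no rate at which culture would change and plans no pooling. At most 40 students per cohort work within a very large service, so a negligible change by month 12 is possible.
- **Trained students will mark their workplace lower, and this will be read as lost confidence.** Nothing in the article predicts it.
- **Respondents rate different organisations.** Staff "from other Queensland Health Hospital and Health Services have the opportunity to undertake" the certificate, while the Sample size section has places filled by staff whom the partner service selects. Who may enrol and who selects need not conflict. If workplaces did differ, the carry-over argument would be weaker, so the two cannot both be pressed.

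**What to change.** Under Quantitative methods:

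1. Limit the motivation and confidence tests and conclusions to ABC and GCOS.
2. State in a clause what each instrument is taken to measure. For the NHS tool, name perceived culture for innovation as a separate outcome, after checking this against the tool itself.
3. Report the NHS tool's three-wave change by cohort, with no claim about participant confidence or motivation.
4. Add one sentence of interpretation: Cohort 2's first NHS wave, in July 2024, was taken 12 months into Cohort 1's two-year program, and any effect of this on the score is unknown.

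The cost is wording only; no data collection changes. The downside is small but should be stated: the confidence and motivation results then have no 12-month follow-up. An analysis by employing service is not recommended, because splitting 30 to 40 participants per cohort that way could leave very small groups.

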### Implementing the codesign process

Codesign of the graduate certificate program began early in the project, with the healthcare organization providing an outline of its aims and objectives for each of the four courses in the program. The university then provided an outline of learning outcomes and scaffolded skill development for each of the courses to the health sector partner to form a basis for starting the codesign process. Once the outlines were agreed upon, course design commenced by codesigning a course profile (subject information). The course profile outlines the course aims, learning outcomes, knowledge and skill development, and assessment criteria. All of these components are codesigned to ensure that the program is responsive to health sector needs. The stakeholder codesign spectrum, shown in Fig. 3, is designed to include more than just consultation and feedback and includes active stakeholder involvement in identifying issues and potential solutions.

**Fig. 3 Fig3:**
[figure not shown]
Spectrum of codesign approach

The codesign spectrum will be implemented at different stages for the four courses in the graduate certificate. Stage 1 of the codesign process involves the development of a course outline and profile by the academic team. Health sector partner approval is then required to proceed to key stakeholder presentations (alumni, HHS experts, HHS educators, academics and university learning and teaching design experts). A review of the feedback and adjustments are then made to the course outline before proceeding. Stage 2 of the codesign process involves the presentation of the adjusted course profile to the Curriculum Advisory Board (CAB) (University and HHS executives governing the LHSI program). Reviews and further adjustments are made, and the manuscript is resubmitted to the CAB for final approval and support for submission to the Dean Learning and Teaching for university approval. Following this, the course will be developed within an online platform. A local project manager coordinated the codesign process through stage 1 and stage 2.

### Evaluating the hybrid type 2 implementation trial

To allow for dual testing of clinical (workforce education) and implementation (academic detailing) interventions and strategies, the project will follow the RE-AIM framework to evaluate the LHSI program. A detailed description of the assessments of the RE-AIM domains is provided in Table 1.

**Table 1 Tab1:** Hybrid type 2 evaluation framework

Reach	LHSI numbers including student participants in the graduate certificate of health service innovation; health sector supervisors, line managers and executive who participate in mentoring, supervision and sponsoring of students; practitioners and key stakeholders who participate in the LHSI program including workshop delivery, roundtables, conferences; and academic practitioners involved in development and delivery
Effectiveness	Students • Knowledge and skill development in health service innovation • Student confidence and motivation development throughout the program • Student confidence and knowledge development for assessment • Student workshop participation, knowledge and skill development • Quantitative information will be collected regarding: ∘ Workshop effectiveness ∘ Confidence and motivation ∘ Satisfaction of content delivery and teaching and learning activities • Qualitative information will be collected regarding: ∘ Satisfaction with course content and delivery ∘ Changes in teaching, learning and assessment reported by students ∘ Innovation and translation knowledge and skill development reported by students Key stakeholders • Codesign process evaluation reported by key stakeholders • Program evaluation **•** Project innovation development evaluation
Adoption	The number of innovation projects implemented throughout the health service Adoption of translational learning within the organization
Implementation	The delivery of the LHSI program including two cohorts through the graduate certificate in health service innovation. The extent of the intended delivery and the number of iterations required through the codesign process. The teaching and learning design strategies and educational tools needed. The facilitators and barriers to implementation of the codesign, curriculum development, cohort delivery, as an indication of the degree of adherence to the prescribed program and to understand the effectiveness and reliability of the program and interventions implemented as intended and whether deviations impact outcomes
Maintenance	The number of innovative strategies implemented into the workplace and positive innovative strategies developed and adapted

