Experience-based codesign (EBCD) is a methodology that actively involves end-users, including consumers and healthcare providers, to design and improve healthcare services [31]. This collaborative methodology prioritizes user experiences and needs by utilizing a participatory action research process that includes the principles of learning theory and narrative-based approaches to drive transformation. The user-centered approach of EBCD ensures that innovations directly address the real challenges faced by individuals in the healthcare system, enhancing the quality of care and increasing the likelihood of successful adoption. The EBCD process typically includes understanding personal experiences, identifying critical touchpoints, engaging in codesign workshops, and reviewing what has been developed. The codesign process allows all stakeholders to make meaningful contributions. For example, in this project, one crucial touchpoint was including authentic assessments that were not predominantly essay writing. The academic team developed assessment prototypes to align with the Australian Qualifications Framework, and health sector partners provided feedback on these prototype assessment tasks, which assisted them in understanding university requirements.

The RE-AIM framework, encompassing Reach, Effectiveness, Adoption, Implementation, and Maintenance, is a comprehensive tool used to assess the impact and sustainability of the implementation process [32, 33]. Particularly beneficial for codesigned education programs on health innovation, RE-AIM is a holistic approach that considers diverse dimensions, including inclusivity in reach, effectiveness in achieving goals, adoption by relevant entities, implementation fidelity, and long-term maintenance [32, 34]. This framework aligns with the principles of codesign, ensuring that interventions are not only effective but also accessible, acceptable, and sustainable over time. In this study, RE-AIM was used to evaluate the graduate certificate program and the knowledge and skill development of the students in the program.

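### Table 1 measures Maintenance as an undated count of strategies implemented, overlapping Adoption and with no continued-use criterion, so that domain cannot show whether projects persisted

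*Protocol article*

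**What the plan says.** The Theoretical framework section states that RE-AIM "is a comprehensive tool used to assess the impact and sustainability of the implementation process". Among the dimensions it lists are "adoption by relevant entities, implementation fidelity, and long-term maintenance".

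The section on evaluating the hybrid type 2 trial says the project will follow RE-AIM and that "A detailed description of the assessments of the RE-AIM domains is provided in Table 1". Table 1 then defines the two domains at issue:

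- Adoption: "The number of innovation projects implemented throughout the health service Adoption of translational learning within the organization".
- Maintenance: "The number of innovative strategies implemented into the workplace and positive innovative strategies developed and adapted". This is the whole row.

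One measure elsewhere in the protocol reaches beyond the end of the program. Under Quantitative methods, the NHS Creating a Culture for Innovation tool is given at the start, "at the conclusion of the four courses of the Graduate Certificate and at 12 months post completion for each cohort", and results are compared across these three points. Table 1 does not mention this measure in the Maintenance row.

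**The concern.** Maintenance should answer what was still in place after the program ended. The row as worded answers a different question, namely how many strategies were put in place, developed or adapted. That is close to what Adoption already asks, and no rule separates a project from a strategy, so one piece of work can score in both rows. The word *positive* also admits items to the second element according to how they turned out.

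At stake is the sustainability conclusion. A healthy Maintenance figure could be reported for a set of projects most of which had stopped, and a reader who trusts the domain name would take it as evidence of lasting change.

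**Working it through.** The plan gives no figure for this domain, so there is none to reproduce. The check compares wording, then the logic of the count, then the calendar.

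**1. The two rows side by side**

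| | Adoption | Maintenance |
|---|---|---|
| First element | number of innovation projects implemented | number of innovative strategies implemented |
| Second element | uptake of translational learning in the organization | positive strategies developed and adapted |
| Time point | none | none |
| Continued-use criterion | none | none |
| Stated link to enrolled students | none | none |

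The first elements are near-duplicates. The second elements differ.

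**2. What the Maintenance count can register**

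Let I be the number of strategies implemented, D the number of positive strategies developed and adapted, and S the number of the implemented ones still operating at some later date, so that 0 ≤ S ≤ I.

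- What the row records depends on I and D only.
- The sustained proportion is S / I.
- For any fixed I and D, S can take any value from 0 to I without changing the reported result. S / I can therefore lie anywhere from 0 / I = 0% to I / I = 100%.

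A cumulative count of things implemented does not fall when one of them stops. Adding a date alone would not cure this: without a criterion of continued operation, the count becomes a total to date.

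**3. Construct against measure**

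The stated construct is sustainability and long-term maintenance. The stated measure is implementation, development and adaptation. *Adapted* may hint at continuing work, but it does not require the strategy to be in use at any given time. The measure does not capture the construct.

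**4. Is a dated measure feasible?**

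Inputs: two-year part-time delivery (first Study design section); cohort starts of July 2023 and July 2024 (Sample size); project end of July 2027 (Project timeline). Completion = start + 24 months; follow-up = completion + 12 months.

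- Cohort 1: July 2023 + 24 months = about July 2025; + 12 months = about July 2026. That leaves about 12 months before the project ends.
- Cohort 2: July 2024 + 24 months = about July 2026; + 12 months = about July 2027. That leaves none.

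A 12-month measure of continued operation fits both cohorts, if only just for the second.

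**The case against.** **The protocol does look past program end.** The NHS tool is repeated 12 months after completion, and the interviews are to gather information on changes over time. A reader might infer from Table 1 that the trial cannot show that anything was sustained. The documents do not support that: the tool can show whether culture scores hold up. It does not record whether a project is still running, and Table 1 does not link it to Maintenance. The point is therefore confined to the Maintenance domain as defined.

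**The rows are not identical.** This stands. Each has a distinct second element, and the overlap concerns the first elements. A reader might also infer that the Maintenance count must equal or exceed the Adoption count. That does not follow, because projects across the service and strategies in the workplace are not defined as the same units.

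**Attribution is a separate matter.** A reader might infer from the phrase "The number of innovation projects implemented throughout the health service" that unrelated projects are counted and that Adoption would be positive even if the program did nothing. That is one reading of the phrase. Table 1 is introduced as the framework for evaluating the LHSI program, so program-linked projects may be what is meant, and nothing in the document establishes what the count would be without the program. What stands is that the row states no link to participants.

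**A condensed article leaves detail to fuller documents, and Fig. 2 is not shown.** This is fair for dates, denominators and eligibility rules, and those gaps alone would not be a finding. It does not rescue the definition: Table 1 is presented as the detailed description, and it fixes the measure as strategies implemented, developed and adapted. A date supplied elsewhere would not turn that into a measure of continued operation.

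**Conclusion.** The Maintenance row is badly specified. As defined, it cannot show whether implemented projects persisted, although the protocol's own account of RE-AIM says that sustainability and long-term maintenance are what is being assessed.

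The documents allow only a logical statement of size: the reported result is compatible with any sustained proportion from 0% to 100%. They give no expected number of projects and no survival rate, so a numerical error cannot be estimated and none is offered.

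The conclusion assumes that *implemented* carries its ordinary sense of having been put in place, not of being still in operation. It affects one of the five RE-AIM domains and leaves the confidence, motivation and culture-tool analyses untouched. The definition should be changed, since the remedy is specific and cheap.

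**What to change.** Keep a single list of projects traceable to LHSI participants, and reword two rows of Table 1:

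- **Adoption:** the number of listed projects implemented by program conclusion. Keep the translational-learning element. Report any service-wide project count as context only.
- **Maintenance:** the number and proportion of those adopted projects still operating at the existing 12-month post-completion point. Discontinued projects stay in the denominator. Delete *positive*, so that a project's result does not decide whether it is counted.

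State in the same row that the 12-month NHS tool is reported alongside as persistence of innovation culture, a different quantity.

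Costs:

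- One extra follow-up item per project. It should be collected through the project list, because the Ethics section describes online anonymous surveys, and answers given there could not be tied to a project.
- The reported figures will probably be smaller than an undated count.
- Cohort 2 reaches its 12-month point at about July 2027, the stated project end. Any late completion would push that follow-up past the project period, so the team should decide in advance how such projects are reported.
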